#### Secondary outcomes

2.4.2

The number of patients and adverse events will be recorded. Adverse events are undesirable signs or symptoms that occur during the study and whose cause may or may not be causal related to the treatment. All adverse events considered possibly, probably or related to the test product will be noted down on the patient's form.^[13]^ The number of patients and adverse events will be recorded.

Serious adverse events are defined as events that are fatal, life-threatening, disabling or result in hospitalization or prolonged stay, or result in malformation, whether related to the test product or otherwise^[13]^

According to previous studies, probiotics are safe and any serious adverse event that could possibly, probably or be related to the test products will be considered unexpected. All unexpected serious adverse events will be reported to the physician. Any serious adverse event that may be related to the test product will immediately lead to discontinuation of the test product.^[13]^

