### Data analysis planning

2.10

Preliminary data indicate that the number of evacuations weekly is 2 or 3 times higher in patients than in control volunteers. The hypothesis is that treatment will likely increase the number of weekly bowel movements from 1 to 3 times to over 4 times a week, while no changes will be seen in the placebo group.

Anova will be used in order to compare continuous variables between the intervention and control groups. Score changes between the intervention and the control groups will be compared by Kruskall–Wallis.

Analysis of adverse events (if any) and the other outcomes will be performed using the Student *t* test and Mann–Whitney *U* test. In all measured will used the intention to treat analysis. The level of significance will be at *P* < .05. The raw data will be input into the statistical software. Statistical analysis will be performed at STATA v.14.2.

All data collected on paper will be marked with a research identification number to avoid identifying the participants and stored in a locked cabinet. Only the author of the research report can access these identified data sets.

The data monitoring committee is not necessary because the statistical analysts will be blind to evaluate the outcomes data.

Volunteers will be instructed to write down any adverse events on the attached form A and if they feel the need to interrupt treatment due to inconvenience that they are unable to continue and write down what the reactions were.

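### The protocol contradicts itself on which adverse events are captured: every event, or those judged related to the product

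*Protocol article*

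**What the plan says.** **Adverse events.** Section 2.4.2 of the protocol defines an adverse event as one "whose cause may or may not be causal related to the treatment". The next sentence sets the recording rule for the patient's form: "All adverse events considered possibly, probably or related to the test product will be noted down". Before and after it, the section says without any causality condition: "The number of patients and adverse events will be recorded". Section 2.10 gives the instruction to participants: "Volunteers will be instructed to write down any adverse events on the attached form A".

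**Serious adverse events.** Section 2.4.2 defines these "whether related to the test product or otherwise". It then treats serious events that are possibly, probably or related to the product as unexpected, on the ground that probiotics are safe. The route it names is: "All unexpected serious adverse events will be reported to the physician".

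**Analysis.** Section 2.10 states: "Analysis of adverse events (if any) and the other outcomes will be performed using the Student" t test and the Mann–Whitney U test. It assigns ANOVA and Kruskal–Wallis to the continuous variables and score changes. The trial has three arms allocated 1:1:1 (2.6).

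**The concern.** Safety is a stated aim of the trial (Introduction), and adverse events, serious adverse events and withdrawals are listed outcomes (Abstract). A safety count is most informative when every event is captured first and causality is judged afterwards. If a relatedness judgement decides what is written down, three things follow:

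- The count depends on a subjective call for which the article names no assessor and no criterion.
- The call falls on symptoms for which it is hardest to make. In people with constipation, intestinal discomfort may come from the disease or from the product.
- What is never written down cannot be restored by any later analysis plan.

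The second issue is the named tests. The t test compares means and Mann–Whitney compares ranks, each between two groups. The quantities here are numbers of patients with an event, a serious event or a withdrawal, in three arms, and 2.10 does not say which pairs are compared.

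**Working it through.** **1. The passages side by side**

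| Item | Where | Causality condition? |
|---|---|---|
| Definition of adverse event | 2.4.2 | None |
| What goes on the patient's form | 2.4.2 | Possibly, probably or related |
| Numbers to be recorded (stated twice) | 2.4.2 | None |
| Participant's instruction, form A | 2.10 | None |
| Definition of serious adverse event | 2.4.2 | None |
| Reporting route for serious events | 2.4.2 | Unexpected, tied to possibly, probably or related |

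The form rule and the participant's instruction cannot both decide which events are counted. The article does not say whether form A and the patient's form are one document, or whether the relatedness rule applies when the diary is transcribed. The repeated sentence about recording numbers does not say which events are numbered. The text therefore leaves the captured set undefined; it does not establish a related-only rule.

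**2. What the relatedness rule would do if it governed the form**

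Let *b* be the expected background events per arm and *e* the excess caused by a probiotic. Let *r_b* and *r_e* (each between 0 and 1) be the shares judged related and so kept.

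- Placebo count: *b* becomes *r_b·b*.
- Probiotic count: *b + e* becomes *r_b·b + r_e·e*.
- Difference: *e* becomes *r_e·e*.

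If the product causes no excess (*e* = 0) and the judgement is blind, both arms are cut by the same factor and no false difference appears. If *r_b* = *r_e*, the ratio between arms is unchanged. The absolute counts, and any true excess, shrink by the share discarded. The documents give neither share, so the loss can be anything from none to all of the events.

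**3. The tests**

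The article gives no adverse event rate, so the risks below are assumptions. For *a* and *b* patients with an event among *n* = 50 per arm (2.1), the pooled t statistic is

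t = (a/n − b/n) / √(s²·2/n), with s² = [a(1 − a/n) + b(1 − b/n)] / (2n − 2).

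For 4 v 0: s² = 4 × 0.92 / 98 = 0.03755; t = 0.08 / √(0.03755 × 0.04) = 2.06 on 98 degrees of freedom; P = .042. The other tests on the same tables (two-sided; Mann–Whitney asymptotic without continuity correction; Boschloo as twice the one-sided value):

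| Events | t | Mann–Whitney | Fisher | Barnard | Boschloo |
|---|---|---|---|---|---|
| 4 v 0 | .042 | .042 | .117 | .044 | .089 |
| 5 v 0 | .022 | .022 | .056 | .024 | .035 |
| 6 v 1 | .051 | .051 | .112 | .061 | .089 |

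The exact tests disagree among themselves, so the gap between t and Fisher is not a measure of error in the t test. The direct measure is type I error when both arms share risk *p*: the sum over all (a, b) of Bin(a; 50, p) × Bin(b; 50, p), taken where P < .05.

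| Assumed risk | t test | Fisher |
|---|---|---|
| 2% | 1.3% | 0.04% |
| 5% | 4.3% | 0.7% |
| 10% | 4.8% | 1.8% |
| 20% | 4.9% | 2.8% |
| 30% | 5.0% | 3.1% |

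At 44 per arm (2.5), simulation with 20,000 runs gives 4.8–6.0% for a single pairwise t test at risks of 5–30%; the highest values are at 10%. Across unadjusted pairs the independence bounds are 1 − 0.95² = 9.75% for two comparisons and 1 − 0.95³ = 14.3% for three. Simulation gives about 8–11% and 11–14%.

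**The case against.** The strongest reply is that the article never says unrelated events go unrecorded. It twice says, without a condition, that adverse events will be recorded, and participants are told to write down any of them. That stands. A reader might infer that only related events are captured and that every unrelated one is lost, but the documents do not settle this. They show a contradiction.

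A second reply is blinding. Section 2.6 says that participants and outcome assessors are blinded and the sachets are identical, so a relatedness call made blind loses events without favouring an arm. This also stands. A reader might suspect uneven filtering because the researcher named for randomisation (2.6) also completes the data form (2.7). The article does not say that this researcher judges relatedness, so uneven filtering is not shown. It is a reason to state that the judgement is made blind.

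Third, the tests. A reader might infer from Fisher's larger P values that the t test makes the safety comparison unreliable. The type I error figures do not support that: the t test stays close to its nominal level, while Fisher's test is well below it when events are few. Two-group tests may also properly be used pairwise in a three-arm trial. What remains is a poor match between tests of means or ranks and numbers of patients with events, and comparisons that are not named. The choice among methods for proportions is largely preference.

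**Conclusion.** The contradiction on which events are captured is real and should be resolved before safety data are entered, because an analysis plan cannot repair it later. The same applies to serious events, where the definition is wider than the only reporting route named. If the relatedness rule governs, the effect is an undercount equal to the share of events judged unrelated. That size cannot be derived from the documents. Given blinded judgement, a false difference between arms is not expected, though a true excess would look smaller in absolute terms.

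The choice of tests is a secondary point of fit, not of validity. At 50 per arm the pairwise t test has an exact type I error of 1.3–5.0% for assumed risks of 2–30%, and at 44 per arm it reaches about 6% at worst in simulation.

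**What to change.** **Main change.** Reconcile 2.4.2 and 2.10. Say that all adverse events and serious adverse events are recorded and counted whatever their judged cause, and that relatedness is a separate attribute assessed blind to allocation. State how form A relates to the patient's form. Reconcile the definition of serious events with the reporting route; which events are reported to the physician is for the investigators to settle.

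**Secondary change.** In 2.10, replace the t and Mann–Whitney tests for these outcomes with the number of patients with at least one event per arm. Do this for adverse events, serious adverse events and withdrawals, with a risk difference and confidence interval for each probiotic versus placebo from a method for proportions. Fisher's test is one conservative option, not the benchmark.

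**Cost.** About one sentence in each section. Participants are already asked to write down any event, so the burden is slightly more data entry. Reported counts will be higher, which the eventual report should explain.

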### Sample size and recruitment

2.5

In order to achieve 80% statistical power (*P* value = .05) between the 3 treatments, 132 patients should be recruited (44 patients per group). As a dropout rate of 15% is expected that will be included in the study 152 participants. A schematic diagram of time schedule of enrolment and interventions of the research groups is summarized in Figure 1.

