### Study design and setting

2.1

This study is parallel and has the structure of superiority working with the hypothesis that the groups that will receive probiotics are more effective than the group that will receive the placebo (constituted of only fibers, vitamins, and minerals which is a conventional treatment for constipation).

Over a 4-week period, a singlecentre, double-blind, randomized, placebo-controlled study of 150 patients (50 patients per group) with functional constipation will be treated using probiotics containing 3 billion CFU of mixed strains probiotics containing 8 billion CFU of mixed strains or placebo.

The study will be conducted in Clinic of Gastroenterology [name] [name], localized in Sorocaba, State of São Paulo, Brazil. Patient recruitment for this study will be carried out through a collaborative effort between the University of Sorocaba and physician [name] that attending in Clinic of Gastroenterology. From the university, a flyer will be sent out via e-mail and letters distributed around Campus or messages texted via cell phone, and social media will also be exploited to promote the study.

The recruitment will be until the date of November 30, 2020. After verbal and written explanation, individuals who agreed to participate in the study will sign the Free and Informed Term of Consent already approved by the Ethics Committee of the University of Sorocaba (Annex B, supplemental digital content).

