**Figure 1 F1:**
[figure not shown]
Flowchart describing study design, sample composition, and experimental protocol. BSFS = Bristol Stool Form Scale, CFU = Colony Forming Unit.

The strategy to achieve the appropriate registration of participants to reach the target sample size will be disseminated on social networks at the University of Sorocaba and poster at the Gastroenterology Clinic Dra [name].

The sample size was calculated based on 2 means and their standard deviations. In preliminary studies, the correlation established using the website openepi.com.

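### The 80% power claimed across three treatments rests on a two-mean calculation, so it supports one pairwise comparison only; the enrolled number is 150 or 152, and neither leaves the required 132 after 15% loss

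*Protocol article*

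**What the plan says.** Section 2.5 (Sample size and recruitment) sets "80% statistical power" at .05 "between the 3 treatments, 132 patients should be recruited (44 patients per group"). It then allows for loss: "As a dropout rate of 15% is expected that will be included in the study 152 participants".

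Later in the same section, after Figure 1, the basis is given: "The sample size was calculated based on 2 means and their standard deviations". The article does not print the two means, the SDs, the sidedness or the pair of arms.

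Section 2.1 (Study design and setting) gives a different enrolment: "150 patients (50 patients per group) with functional constipation". It describes a superiority trial of the probiotic groups against placebo, and it describes that placebo as "constituted of only fibers, vitamins, and minerals which is a conventional treatment for constipation".

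Section 2.10 (Data analysis planning) expects the treated groups to rise from 1–3 to more than 4 movements a week, "while no changes will be seen in the placebo group". It plans ANOVA for continuous variables. The Introduction and the Discussion add a further aim: whether 8 strains do better than 3.

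**The concern.** The power statement and its method describe different things. A two-mean calculation fixes the power of one contrast between two arms. The trial has three contrasts of interest: each probiotic against placebo, and 8 against 3 strains. Nothing in the stated calculation carries 80% over to all of them.

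The numbers around it also disagree. There are two enrolment totals, and neither leaves the required evaluable number once the plan's own dropout rate is applied. The expected placebo course does not fit the plan's own description of what the placebo is.

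What is at stake is interpretation. If the trial reports 80% power across three arms, a null result for one product, or for 8 against 3 strains, will be read as evidence of no difference when the calculation never covered that comparison.

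**Working it through.** **Inputs.** From section 2.5: power 80%, alpha .05, 44 per group (132 in all), 15% dropout, 152 enrolled, two-mean basis. From section 2.1: 150 enrolled, 50 per group. From section 2.6: 1:1:1 allocation. The means and SDs are not given, so the 44 itself cannot be reproduced.

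**1. Dropout arithmetic**

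- The plan's figure: 132 × 1.15 = 151.8, rounded up to 152. This reproduces it.
- Number needed so that 132 remain after 15% loss: 132 / (1 − 0.15) = 155.3, so 156 (52 per group).
- What 150 leaves: 150 × 0.85 = 127.5 (42.5 per group).
- What 152 leaves: 152 × 0.85 = 129.2 (43.1 per group).
- Both are below 132. Also, 152 / 3 = 50.67, so 152 does not divide into three equal groups.

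**2. The effect implied by 44 per group.** Assume a two-sided .05 two-sample *t* test for one pair. Setting its power to 80% at n = 44 gives a standardised difference d = 0.604. The normal approximation, (1.960 + 0.842) × √(2/44), gives 0.597; a one-sided reading gives 0.530 by the same approximation. This d is back-solved to see how power moves. It is not the trial's own planning effect.

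**3. Cost of the dropout slip and the mismatch.** One pair, two-sided .05, d = 0.604:

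| Evaluable per group | Source | Power |
|---|---|---|
| 44 | stated target | 80.0% |
| 43.1 | 152 less 15% | 79.1% |
| 42.5 | 150 less 15% | 78.6% |

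The loss is about 1 point.

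**4. What 44 per group gives for three-arm aims**, same d:

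| Criterion | Power |
|---|---|
| Both probiotics superior to placebo, each at .05 (the two contrasts share the placebo arm, correlation 0.5) | 69% |
| One pair, alpha split over two comparisons (.025; an assumption) | 71% |
| ANOVA, arm means (0, d, d) | 83% |
| ANOVA, arm means (0, d/2, d) | 71% |

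The ANOVA rows use the noncentral F with 2 and 3(n − 1) degrees of freedom and noncentrality n × Σ(mean − grand mean)². At 42.5 per group they become 82% and 69%.

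**5. Placebo response.** The planning difference is the active gain minus the placebo gain. If placebo achieves a share f of the planned difference (assumed range 25% to 50%), the difference becomes d(1 − f). One-pair power at 44 per group is then:

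- f = 0: 80%
- f = 0.25: d = 0.453, power 56%
- f = 0.50: d = 0.302, power 29%

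**The case against.** A reader might infer that the 80% is simply not delivered. The article does not support that. With no means, SDs or sidedness, any power figure rests on a back-solved effect.

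Under the pattern closest to the stated hypothesis, with both probiotics working fully and placebo unchanged, the planned ANOVA has about 83% at 44 per group and about 82% even at 42.5. On that reading, 80% for an overall test across three groups is met. This stands. However, the stated calculation is not an ANOVA calculation, and a significant overall test does not show which product works or whether 8 strains beat 3.

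The 69% applies a both-must-succeed criterion, and the 71% per pair applies an alpha split; the article sets neither. They show scale only.

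It is also true that the dropout slip and the 150/152 mismatch cost about 1 point of power. They need correcting because the text contradicts itself and misses its own target, not because they endanger the trial.

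Finally, a reader might say that the calculation assumes a placebo that does not change. Section 2.10 states this as the hypothesis, and nothing names it as an input. The two means could already allow for a placebo response. What remains is the conflict between sections 2.1 and 2.10. The absence of the inputs from a condensed article is not in itself a fault.

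**Conclusion.** The point holds in a limited form. As written, the calculation supports 80% for one pairwise comparison at .05, and the claim across three treatments does not follow from it. The two enrolment totals contradict each other, the dropout inflation uses the wrong operation, and both totals miss the required 132 (about 127 and about 129 evaluable).

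The arithmetic slips are small, about 1 point for one pair. The choice of comparison matters more: from about 83% down to about 69%, depending on what counts as success. The placebo assumption could matter most, with one-pair power at 56% to 29% if placebo reaches 25% to 50% of the planned difference.

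All the power figures assume a two-sided .05 calculation for one pair with a back-solved d of about 0.60, and the placebo range is an assumption. The contradictions in the text and the dropout arithmetic need no such assumption.

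**What to change.** - Give one enrolled number in sections 2.1 and 2.5.
- Either correct the inflation to 132/0.85 (156, or 52 per group), or keep the smaller number and restate what it yields. With 150 enrolled, about 127 are evaluable, and power is about 78–79% for the pair that had 80% at 44 per group.
- In section 2.5, replace the reference to all three treatments with the single comparison that the 80% refers to, and give the means, SDs and sidedness actually entered. The 0.60 used here should not be printed as the planning effect.
- State that the other comparisons, including 8 against 3 strains, were not separately powered by this calculation.
- Reconcile sections 2.1 and 2.10 on the placebo: express the planning effect as a between-arm difference that allows for improvement on the fibre placebo.

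The cost is a few restated sentences and slightly less favourable figures. No extra patients are required if the smaller number is kept and its power is stated.

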**Figure 1 F1:**
[figure not shown]
Flowchart describing study design, sample composition, and experimental protocol. BSFS = Bristol Stool Form Scale, CFU = Colony Forming Unit.

The strategy to achieve the appropriate registration of participants to reach the target sample size will be disseminated on social networks at the University of Sorocaba and poster at the Gastroenterology Clinic Dra [name].

The sample size was calculated based on 2 means and their standard deviations. In preliminary studies, the correlation established using the website openepi.com.

### Data handling and record keeping

2.7

The data from the volunteers’ records will be entered in excel format and the records will be stored in a safe place in order to prove the study.

A data collection form will be used to record patient data for all participants and completed by the pharmaceutical researcher (FCRM), who will also enter the data into a database. The results will checked, in duplicate, to ensure the quality of the measured outcomes.

### Volunteer withdrawal

2.8

The number of volunteer who dropped out of the study due to the presence of adverse events.

### Ethical and regulatory aspects

2.9

The study protocol was approved by the Ethics Committee of the University of Sorocaba. The project is filed under the CEP-Single CAAE Number: 84003418.9.0000.5500 and was approved on 09/17/2018.

These documents state that volunteers’ informed consent is an essential precondition for participating in the clinical study. The study will begin only after approval by the local Ethics Review Board of the University of Sorocaba.

### Data analysis planning

2.10

Preliminary data indicate that the number of evacuations weekly is 2 or 3 times higher in patients than in control volunteers. The hypothesis is that treatment will likely increase the number of weekly bowel movements from 1 to 3 times to over 4 times a week, while no changes will be seen in the placebo group.

Anova will be used in order to compare continuous variables between the intervention and control groups. Score changes between the intervention and the control groups will be compared by Kruskall–Wallis.

Analysis of adverse events (if any) and the other outcomes will be performed using the Student *t* test and Mann–Whitney *U* test. In all measured will used the intention to treat analysis. The level of significance will be at *P* < .05. The raw data will be input into the statistical software. Statistical analysis will be performed at STATA v.14.2.

All data collected on paper will be marked with a research identification number to avoid identifying the participants and stored in a locked cabinet. Only the author of the research report can access these identified data sets.

The data monitoring committee is not necessary because the statistical analysts will be blind to evaluate the outcomes data.

Volunteers will be instructed to write down any adverse events on the attached form A and if they feel the need to interrupt treatment due to inconvenience that they are unable to continue and write down what the reactions were.

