#### Primary outcomes

2.4.1

Changes in the frequency of bowel movements and in stool quality will be noted down in a table which the patient must fill out with information about daily frequency and type of stool (on a scale of 1–7 of the Bristol scale, or whether there was no bowel movement).

Stool form will be assessed using the BSFS (Bristol Stool Form Scale), a simple tool for estimating intestinal transit time.^[5]^ The BSFS classifies stools into 7 categories, including type 1, separate hard lumps, like nuts; type 2, sausage-shaped, but lumpy; type 3, like a sausage but with cracks on the surface; type 4, like a sausage or snake, smooth and soft; type 5, soft blobs with clear-cut edges; type 6, fluffy pieces with ragged edges, a mushy stool; type 7, watery, no solid pieces.^[5]^ These types are categorized into slow transit (types 1 and 2), normal transit (types 3–5), and fast transit (types 6 and 7).

The metric of analysis will be the comparison between 0 and 30 days, considering that the number of effective bowel movements over 4 times a week is an effective value for the treatment and the quality of the stools from 3 to 5.

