## Discussion

3

This study shall determine whether the combination of Lactobacillus and Bifidobacterium strains can improve functional intestinal constipation due to the action of bacterial flora and thereby increase the frequency of intestinal motility and improve the quality of faces.

Therefore, the combination of different strains must be evaluated, as the species may differ in their effects, as well as in aspects related to their safety.

Clinical trials are essential to assess functional therapy for constipation and identify desirable therapeutic alternatives to increase treatment effectiveness and compliance levels.

This study combining 8 strains of probiotics, as measured by benefits to the gastrointestinal system, has not yet been evaluated in a parallel group with probiotics containing 3 strains, to determine which combination will have the best action in reducing constipation, using fibers as a placebo.

A limitation of this study is that results will be based on the self-reporting of symptoms by selected volunteers with functional constipation as opposed to direct observation.

The placebo will contain no probiotic strains (only fibers, vitamins, and minerals) so that the desired effect of a significant difference in the treatment of constipation can be attributed solely to the probiotics.

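### The primary outcomes are assigned three-group tests at a flat 5%, and these cannot show what the trial sets out to show: that a probiotic product beats placebo

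*Protocol article*

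**What the plan says.** - **Hypothesis** (section 2.1, Study design and setting): a superiority trial in which "the groups that will receive probiotics are more effective than the group that will receive the placebo". The Discussion adds a comparison of the two products, "to determine which combination will have the best action in reducing constipation".
- **Primary outcomes** (section 2.4.1): "Changes in the frequency of bowel movements and in stool quality will be noted down in a table". Frequency and stool quality appear together, unranked. The time frame is fixed: "The metric of analysis will be the comparison between 0 and 30 days".
- **Main tests** (section 2.10, Data analysis planning): "Anova will be used in order to compare continuous variables between the intervention and control groups". For changes from baseline the section turns to a rank test across the arms: "Score changes between the intervention and the control groups will be compared by Kruskall–Wallis".
- **Two-group tests** (section 2.10): the t and Mann–Whitney tests have a separate place, in a sentence that begins "Analysis of adverse events (if any) and the other outcomes will be performed using the Student".
- **Level** (section 2.10): "The level of significance will be at *P* < .05", with no distinction between outcomes or comparisons.
- **Sample size** (section 2.5): 44 per group for 80% power, calculated from two means and their standard deviations, whose values are not printed.

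**The concern.** The stated question consists of directional comparisons with placebo. The tests assigned to the primary data ask only whether the three arms differ in some way. A significant result could come from one product against the other, or from a product that does worse than placebo, and would still meet the stated criterion. The sample size rests on a comparison of two means, and the analysis section fixes no such comparison for the primary outcomes.

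With two primary outcomes each tested at 5%, the trial-wide chance of a false-positive result also depends on a success rule that the protocol does not state. At stake is whether a significant result could support the superiority claim at all, and at what error rate.

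**Working it through.** **1. The plan's own figure.** The 44 per group cannot be derived forward, because no means or SDs are given. Back-solving the two-means formula at two-sided .05 and 80% power:

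n = 2(1.960 + 0.842)² / d² = 15.70 / d², so d = √(15.70/44) = 0.597.

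This is an implied value, not one that the protocol states. The exact t calculation gives 0.604.

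**2. What a significant F test shows.** The noncentrality is λ = N × (variance of the three true means)/σ², with N = 132.
- Both products better than placebo, means (0, d, d): variance 2d²/9.
- One product worse than placebo and the other equal to it, means (0, −d, 0): variance 2d²/9.

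In both cases λ = 132 × 2 × 0.597²/9 = 10.45. On 2 and 129 degrees of freedom at .05, power is 82% in both. The test cannot tell the hoped-for result from its opposite.

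**3. Error rate under no effect anywhere.** One omnibus test on one outcome gives 5.0%. Two independent omnibus tests, either sufficient, give 1 − 0.95² = 9.75%. Simulation with three arms of 44, normal data and 20,000 trials per setting gives the chance of at least one P < .05:

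| Procedure | Correlation 0 | 0.3 | 0.6 |
|---|---|---|---|
| Omnibus test on each of two outcomes | 9.7% | 9.7% | 8.7% |
| Ungated placebo pairs, two outcomes | 17.4% | 17.1% | 15.4% |
| Ungated, all three pairs, two outcomes | 22.9% | 22.6% | 20.5% |

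A repeat with 80,000 trials per setting agreed to within half a percentage point. Only the first row describes tests that the protocol assigns to primary-type data. The correlation between outcomes is assumed.

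**4. Use of baseline.** Let r be the assumed correlation between day 0 and day 30, with equal variances σ². The change score has variance 2(1 − r)σ² and ANCOVA has (1 − r²)σ². The ratio is (1 + r)/2 = 0.65, 0.75, 0.85 at r = 0.3, 0.5, 0.7, so ANCOVA variance is 35%, 25%, 15% lower.

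**5. Power of the proposed contrasts.** Start from a change-score comparison with 80% power (d = 0.604, 44 per arm, two-sided .05). Without ANCOVA, testing at .025 lowers this to 71%. With ANCOVA the effective effect is 0.604/√((1 + r)/2):

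| r | Effective d | Power at .025 (first Holm step) | Power at .05 (first in a fixed sequence) |
|---|---|---|---|
| 0.3 | 0.749 | 89% | 94% |
| 0.5 | 0.698 | 84% | 90% |
| 0.7 | 0.655 | 78% | 86% |

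The first Holm step breaks even near (1 + r)/2 = (2.802/3.083)² = 0.826, that is r of about 0.65. Here 2.802 = 1.960 + 0.842 and 3.083 = 2.241 + 0.842.

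**The case against.** **Pairwise tests may follow.** ANOVA followed by pairwise comparisons is routine, and a condensed article can leave contrasts and multiplicity to an analysis plan that is not shown. This stands as far as it goes: the absence of such detail is not the finding. The finding is that the text pairs three-group tests at one flat threshold with a hypothesis of superiority over placebo.

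**A reader might infer a 15–23% error rate.** The documents do not support that. Section 2.10 names the t test and Mann–Whitney for adverse events and the remaining outcomes. Ungated pairwise testing of the primary outcomes is therefore an inference, and those rates show only what would follow if the gap were filled that way.

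**Even 9–10% needs an assumption.** It holds only if either outcome suffices. If both had to be significant, there would be no inflation across outcomes. The protocol states neither rule.

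**A reader might infer that the baseline is ignored.** It is not. The day 0 to day 30 comparison in section 2.4.1 and the score changes in section 2.10 both use it. What remains is a loss of efficiency, not an error.

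**A reader might infer that stool quality must lose its primary status.** That is a design trade-off and is not needed. A rule requiring both outcomes, or a fixed order, also controls the error.

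**Conclusion.** The concern holds in this form: the tests named for the primary data do not answer the superiority question, and a significant result from them would not establish that either product beats placebo. This limb needs no assumption beyond three arms; the 82% figure that illustrates it rests on the back-solved effect size.

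The error-rate limb is conditional. It is about 9–10% instead of 5% if success on either outcome is enough, at outcome correlations of 0 to 0.6, and there is no inflation across outcomes if both are required. The baseline limb is a missed gain of 15–35% in variance relative to a change score, at assumed correlations of 0.7 down to 0.3. Section 2.10 also leaves unclear which of its tests applies to which primary outcome.

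**What to change.** Before unblinding, rewrite section 2.10 as follows.

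1. For weekly bowel-movement frequency, replace the omnibus test as the decision rule with an ANCOVA of the day-30 value on arm and day-0 value.
2. Pre-specify two contrasts, 8-strain versus placebo and 3-strain versus placebo. Control them at a two-sided family-wise 5% by Holm or by a fixed sequence with the order stated. Report each estimate with its 95% confidence interval.
3. State whether success requires both primary outcomes. If it does not, give stool quality a place in the testing order.
4. Test 8 versus 3 strains only afterwards.

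**Cost.** No new patients, visits or data are needed. Items 1, 2 and 4 change the analysis wording only. Item 3 is a design decision for the sponsor. Under Holm, the stricter first threshold is offset by ANCOVA at moderate baseline correlation (89% and 84% power at 0.3 and 0.5) but costs slightly from about 0.7 upward (78% against 80%). A fixed sequence avoids that loss for the first contrast, but the second can be tested only if the first succeeds.
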